## Abstract

**Background:**

Climate extremes in Africa threaten the food security of war-affected refugees, who often experience mental health challenges that hinder their capacity for agricultural adaptation. Cost-effective, climate-smart farming interventions are crucial for addressing food insecurity in humanitarian contexts, yet evidence on their effectiveness is limited, and the potential benefits of integrating them with mental health interventions remain unexplored. We hypothesize that the success of agricultural interventions, especially under adversity, is influenced by mental health and psychological functioning.

**Methods:**

This study employs a three-arm, parallel-group, cluster-randomized controlled trial (cRCT) in the Nakivale refugee settlement, Uganda. Thirty villages within the settlement will be randomized in a 1:1:1 allocation ratio to one of three conditions: Enhanced Usual Care, a Home Gardening Intervention (HGI) or HGI combined with the peer-delivered psychosocial intervention Self-Help Plus (SH + HGI). A total of 900 refugee mothers and their children (aged 3–4 years) will be enrolled, with 30 dyads per village. The primary outcome is food insecurity at 12 months post-intervention, assessed using the Food Insecurity Experience Scale (FIES). Secondary outcomes include dietary diversity, child malnutrition and mothers’ psychological distress. Data will be collected at baseline, 3-month and 12-month follow-ups. Primary analyses will use an intention-to-treat (ITT) approach.

**Discussion:**

This study will shed light on the role of mental health in agricultural adaptation for food security, evaluating the efficacy of scalable, cost-effective interventions in a refugee setting. The findings will have implications for the design and implementation of integrated food security and mental health programs in humanitarian and other resource-constrained settings.

**Trial registration:**

ClinicalTrials.gov NCT06425523. Registered on 24 May 2024.

**Supplementary Information:**

The online version contains supplementary material available at 10.1186/s13063-025-09042-y.

## Administrative information

Note: the numbers in curly brackets in this protocol refer to SPIRIT checklist item numbers. The order of the items has been modified to group similar items (see http://www.equator-network.org/reporting-guidelines/spirit-2013-statement-defining-standard-protocol-items-for-clinical-trials/).

Role of sponsor {5c}	The sponsor and funder have had no role in the design or submission of this protocol. They will have no role in the collection, management, analysis, and interpretation of data.

## Introduction

### Background and rationale {6a}

Climate change poses significant challenges across Africa, particularly for populations dependent on rain-fed agriculture. These communities face increasingly frequent and severe climate-related shocks, such as droughts and floods [1–3], which threaten food security and negatively impact both physical and mental health [4–6]. The situation is further complicated in regions affected by conflict and displacement, where fragile food systems and limited resources exacerbate vulnerabilities [7, 8]. Refugee settlements, in particular, are highly susceptible to climate extremes and their inhabitants face significant challenges in establishing self-reliant livelihoods [9, 10]. Furthermore, exposure to armed conflict and displacement increase mental health problems, which can hinder adaptive capacities [11, 12]. These interconnected issues create a cycle of adversity, resource scarcity, poor mental health and impaired adaptation [13–15].

Rigorous evaluations of interventions aimed at enhancing refugee resilience are crucial for sustainable development amidst climate change [3]. However, there is a lack of systematic research on effective strategies to integrate mental health support with climate-smart interventions, especially among vulnerable populations [16–18]. While the international community acknowledges climate-related malnutrition and invests in agricultural interventions [19, 20], and there is increasing awareness of the mental health gap in low- and middle-income countries [21–23], empirical evaluations of agricultural interventions in humanitarian crises remain limited [24, 25], and the role of mental health in agricultural adaptation is largely unexamined [26, 27].

We contend that successful agricultural adaptation to climate change relies not only on material resources and technical knowledge, but also on individuals’ psychological capacities to implement and maintain these practices [28, 29]. Refugees possess essential psychological skills for sustainable livelihoods, including the ability to learn, adapt, commit to long-term goals and engage in collaborative efforts [30, 31]. However, these skills are often compromised by mental health problems stemming from prolonged exposure to stress and adversity. This can lead to a state of allostatic overload, which disrupts cognitive functions and alters behaviors crucial for effective adaptation [32–35]. Therefore, we posit that addressing mental health will improve psychological functioning, thereby enhancing adaptive capacity [36–38].

To test this, this study aims to evaluate the impact of a climate-resilient, sustainable and scalable Home Gardening Intervention (HGI) on food security among war refugees in Nakivale refugee settlement, Uganda. Simultaneously, the study will evaluate whether enhancing participants’ mental health using the safe, cost-effective and validated psychosocial intervention Self-Help Plus (SH +) [39] can amplify the expected positive impact of HGI on food security.

## Objectives {7}

Our trial aims to test two main hypotheses:

H1: Participants in the villages allocated to the stand-alone Home Gardening Intervention will experience significantly improved food security at the 12-month endpoint, compared to participants in the control group.

H2: Participants receiving SH + in combination with HGI will exhibit superior food security outcomes compared to those receiving HGI alone.

## Trial design {8}

The 30 participating villages within the Nakivale refugee settlement will be the unit of randomization and will be assigned to one of three arms: (1) Enhanced Usual Care (EUC), (2) Home Gardening Intervention (HGI) or (3) a combined Self-Help Plus and Home Gardening Intervention (SH + HGI). To account for baseline differences associated with settlement patterns of recent arrivals, the randomization will be stratified and staggered, with villages allocated in three phases (see section on Participant timeline {13} for details). The trial is designed to demonstrate the superiority of HGI, and particularly SH + HGI, compared to EUC in improving food security outcomes at 12 months post-intervention. The cluster-randomized controlled trial (cRCT) design is essential due to the nature of the interventions, which are delivered at the community level, and to minimize the risk of contamination between the intervention groups that could arise from individual randomization within the same village.

## Methods: participants, interventions and outcomes

### Study setting {9}

This study will take place within the Nakivale refugee settlement, located in southwestern Uganda, Isingiro District. Nakivale is the second-largest refugee camp in Uganda, hosting over 216,000 individuals spread across 79 villages [40, 41]. The inhabitants face significant challenges due to extreme weather patterns, including heatwaves and arid land during dry periods, as well as devastating floods that damage homes and agricultural production during the rainy season [9]. The camp also grapples with numerous agricultural obstacles, including a lack of livestock and restricted access to diverse crops and agricultural training [42]. Food insecurity and mental health issues are major concerns, with high rates of malnutrition among women and children, limited dietary diversity, a strong dependence on external food aid [42] and a substantial proportion of the population suffering from conditions such as generalized anxiety disorders, posttraumatic stress disorder and major depressive disorder [43]. These conditions make Nakivale a particularly relevant setting to study the interplay between climate resilience, food security and mental health.

### Eligibility criteria {10}

The study will be conducted in 30 villages within the Nakivale refugee settlement. Villages were selected based on sufficient access to water for manual irrigation and land for agriculture. Highly urbanized villages and those currently participating in similar programs were excluded. Refugee mothers residing in these selected villages are eligible to participate if they meet the following inclusion criteria: having a child aged 3–4 years, having access to a plot of land suitable for farming, being able to speak and understand Kiswahili, being 18 years of age or older and not planning to move from the settlement within the next 12 months (the study duration). Furthermore, mothers must exhibit at least moderate levels of psychological distress to be included, defined as a score of five or higher on the Kessler 6 (K6) psychological distress scale [44].

Mothers will be excluded if they present an imminent risk of suicide, as assessed through a structured protocol incorporating the suicidality subscale of the Mini International Neuropsychiatric Interview [45]. Additional exclusion criteria include observable signs of psychosis, manic behaviors or intellectual disability that would impede the ability to understand and follow intervention instructions or participate in group sessions. Participants will also be excluded if the mothers express knowledge of their child’s cognitive or developmental impairment, or if the child does not live with the parent who is eligible to take part in the intervention. In the event that a prospective participant has multiple children within the age range of 3–4 years, the index child will be selected by asking the mother which child had their birthday most recently. Both mother and child must meet the eligibility criteria, and provide consent/assent, to be included.

Twenty model farmers will be selected based on their agricultural experience, standing in the community and willingness to participate in training and to provide ongoing support to participants. Self-Help Plus (SH +) facilitators will be selected based on prior working experience in the refugee settlement, social skills, proficiency in both Kiswahili and English and a minimum of secondary education.

### Who will take informed consent? {26a}

Informed consent will be obtained from all participating mothers by trained local enumerators, supervised by the on-site principal researcher. The enumerators will undergo thorough training on the screening, consent procedures and ethical considerations involved in the study. The enumerators will present an informed consent form to all eligible participants, explaining the purpose of the study, the procedures involved, the potential risks and benefits of participation, data confidentiality and the participants’ right to withdraw from the study at any time without penalty. Mothers will be asked to provide parental consent for their child’s inclusion in the study, and the children will be asked to assent. Literate participants will provide their consent by signing the informed consent form. For participants who are illiterate, a thumbprint will be used as a valid form of consent, with a witness present during the consent process.

### Additional consent provisions for collection and use of participant data and biological specimens {26b}

No biological specimens will be collected in this trial.

## Interventions

### Explanation for the choice of comparators {6b}

This study employs a three-arm design to evaluate the effectiveness of a Home Gardening Intervention (HGI) alone and in combination with a mental health intervention (SH +). The Enhanced Usual Care (EUC) arm serves as a control, providing a benchmark for comparison while offering a higher level of support than a simple waitlist condition, thus mitigating potential nocebo effects. Participants in the EUC arm will also receive the HGI training and materials after the final 12-month data collection time point, ensuring they are not disadvantaged by participating in the control group. The HGI arm is designed to assess the impact of climate-smart agricultural practices on food security. The combined SH + HGI arm allows us to test the hypothesis that addressing mental health can enhance the effectiveness of agricultural interventions in this refugee population. This design allows for a direct comparison between the interventions and the control, as well as an assessment of the potential added value of integrating mental health support with agricultural training.

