### Intervention description {11a}

Participants will be randomly assigned to one of three groups: EUC, HGI or a combined Self-Help Plus and Home Gardening Intervention (SH + HGI). In the SH + HGI group, participants will receive the Self-Help Plus intervention before starting the Home Gardening Intervention.

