#### Primary outcome

The primary outcome of this study is food insecurity, which will be measured using the Food Insecurity Experience Scale (FIES) [50] at 12 months post-intervention. The FIES consists of eight questions addressing self-reported food-related behaviors and experiences associated with increasing difficulties in accessing food due to resource constraints. The FIES is unique as it is the most widely used method for evaluating food security at the household or individual level that allows for global comparability [50, 51]. The analysis metric will be the change in the FIES score from baseline to the 12-month follow-up, and the method of aggregation will be the median FIES raw score for each group.

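### H2 validly tests the added effect of SH+ on top of HGI, but with no SH+-only arm it cannot show that SH+ amplifies HGI

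*Protocol article*

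**What the plan says.** The design has three arms: "Thirty villages within the settlement will be randomized in a 1:1:1 allocation ratio to one of three conditions", "with 30 dyads per village". The arms are EUC, HGI and SH+HGI (Trial design {8}; Intervention description {11a}). SH+ is never given without HGI.

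The second main hypothesis is worded as a simple comparison: "Participants receiving SH + in combination with HGI will exhibit superior food security outcomes compared to those receiving HGI alone" (Objectives {7}). Statistical methods {20a} tests it by the pairwise contrast of HGI with SH+HGI.

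The text around H2 goes further in three places:
- Background and rationale {6a}: the study will evaluate whether SH+ "can amplify the expected positive impact of HGI on food security".
- Explanation for the choice of comparators {6b}: the combined arm "allows us to test the hypothesis that addressing mental health can enhance the effectiveness of agricultural interventions in this refugee population".
- Discussion: SH+ is said to be capable of making HGI more effective by improving participants' well-being.

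Section {6b} also uses a weaker term a few lines later, when it speaks of the potential added value of integrating mental health support with the agricultural training.

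The primary outcome, FIES, consists of "eight questions addressing self-reported food-related behaviors and experiences" (Primary outcome). Participants are not blinded; data collectors are (Who will be blinded {17a}).

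**The concern.** To say that SH+ amplifies HGI, or makes an agricultural intervention more effective, is to say that the effect of HGI is larger when SH+ is present. That is a statement about an interaction. The H2 contrast is not an interaction. It also contains whatever SH+ would do to food security in mothers who receive no gardening programme, and this trial has no such group given SH+.

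On the protocol's own reasoning that second component need not be zero. Section {6a} presents the psychological capacities to be restored as general ones that support livelihoods, and Eligibility criteria {10} requires every mother, in every arm, to have access to farmable land. SH+ could therefore help without HGI. Because FIES is self-reported by unblinded mothers, and those in SH+HGI attend five extra group sessions, part of a difference could also lie in how experience is reported. Blinding the data collectors does not remove that.

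H2 is one of two main hypotheses, and the results are meant to inform humanitarian programming. That SH+ makes gardening programmes work better and that SH+ improves reported food security whether or not people garden are different findings, with different consequences for where SH+ should be offered.

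**Working it through.** **Inputs from Sample size {14}, the abstract and {20a}.** 30 villages at 1:1:1, so 10 per arm and J = 20 per pairwise contrast; P = 0.5; 30 dyads per village less 20% attrition, so n = 24; ICC 0.01; variance explained 50% at individual level and 20% at cluster level; alpha 0.05 two-sided; power 95%. One cluster-level covariate is assumed, so df = 20 − 1 − 2 = 17.

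**Step 1: reproduce the plan's figure.** For a two-level cluster-randomised design,

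SE = √[ICC(1 − R²cluster)/(P(1 − P)J) + (1 − ICC)(1 − R²indiv)/(P(1 − P)Jn)]

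= √[0.01 × 0.80/5 + 0.99 × 0.50/(5 × 24)] = √[0.001600 + 0.004125] = 0.0757.

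Minimum detectable difference = (t₀.₉₇₅,₁₇ + t₀.₉₅,₁₇) × SE = (2.110 + 1.740) × 0.0757 = 0.291 SD. This matches the stated 0.291. Noncentral-t power at 0.291 is 95.2%. The sample size is not in question.

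**Step 2: what H2 estimates.** Write effects as improvements in food security, in SD units on the additive scale of the planned model:

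| Arm | Mean |
|---|---|
| EUC | m |
| HGI | m + h |
| SH+HGI | m + h + s + i |

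Here s is the effect of SH+ without HGI and i is the interaction, that is, amplification. H1 estimates h. H2 estimates s + i. Three arm means cannot determine four quantities, and m and h take up two of them. Only the sum s + i is identified, whatever the sample size.

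For example, H2 equals 0.291 for (s, i) = (0, 0.291), for (0.291, 0), and for (0.40, −0.109), where SH+ would weaken HGI. A simulation of village means with 20,000 replicates gave rejection rates of 95.2% for the pure interaction, 95.2% for the purely additive effect and 95.4% for an even split.

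**Step 3: how often H2 is significant with i = 0.** The protocol gives no value for s, so a range is shown (SE 0.0757, df 17, two-sided 5%):

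| Assumed s (SD) | Chance that H2 is significant |
|---|---|
| 0 | 5% |
| 0.10 | 24% |
| 0.15 | 46% |
| 0.20 | 70% |
| 0.25 | 88% |
| 0.291 | 95% |

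**Step 4: whether the other planned analyses separate s from i.** The 3-month K6 check shows whether distress fell, not whether HGI worked better because of it. HDDS and HAZ, compared between the same two arms, also estimate a sum of the form s + i. Moderation by baseline distress {20b} is an exploratory comparison across a characteristic that was not randomised.

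**The case against.** The strongest reply is that hypothesis, test and at least one statement of purpose already agree. H2 in {7} is plain superiority, {20a} tests that, and {6b} itself speaks of added value. The stronger verbs sit in rationale prose, some of it hedged, and could be read loosely as saying that the programme does better with SH+ added. An add-on design also answers the question an implementer would ask. All of this stands as a defence of H2 as worded and of the choice of arms. It does not rescue {6b}, which states as a property of the design that it tests enhancement of the agricultural intervention.

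Four stronger readings are tempting, and the documents do not support them.

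- *H2 is invalid.* It is not; only the interpretation beside it goes too far.
- *A positive H2 could be mere reporting.* A shift in self-report is possible for FIES, but HAZ is measured with a stadiometer, and reporting cannot explain a difference there. HAZ still does not separate s from i.
- *Nothing in the trial measures gardening.* The list of exploratory domains is explicitly not exhaustive. The full list is in Supplementary Table S1, which is not shown, and the article does not say what the garden visits record.
- *A garden score compared between SH+HGI and HGI would settle the matter.* All mothers have farmable land, so SH+ alone could raise cultivation, and that contrast is again s + i. If the visiting staff recorded it, it would also come from people who help to deliver HGI.

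Nor is the missing arm a cheap omission. The interaction has an SE √2 times that of a pairwise contrast, 0.107 with 10 villages per arm (40 in all). Power for an interaction of 0.291 SD would then be 75%. With the present 30 villages spread over four arms it would be 62%. Recruitment is complete (Trial status).

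**Conclusion.** The point holds as one of interpretation. H2 as worded is validly tested, and its stated power reproduces. The contrast identifies only the sum of a direct SH+ effect and the interaction, so a significant H2 cannot support the statements in {6a} and {6b} that SH+ amplifies HGI or makes agricultural interventions more effective. That conclusion is algebraic and needs no numerical assumption.

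The size does need one. With no amplification at all, H2 would be significant between 24% and 95% of the time for SH+-only effects from 0.10 to 0.291 SD. The upper end has SH+ alone produce the whole design effect, so it is one assumed value and should not be quoted as the expected rate. That a positive H2 would be written up as synergy is an inference, though it follows directly from the wording of {6b}.

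**What to change.** 1. In {6a} and {6b}, and in the matching sentence of the Discussion, describe what H2 estimates as the added effect of SH+ when given on top of HGI, in line with the added-value wording that {6b} already contains.
2. State that synergy with HGI and a direct effect of SH+, including one on self-reported FIES, cannot be distinguished in this design.
3. State in advance that a positive H2 will not be reported as evidence of amplification.

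H2, its test, the sample size and data collection stay as they are. No arm, visit or instrument is added. The cost is a narrower headline claim, and the wording can be settled before outcome data are seen.

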### Intervention description {11a}

Participants will be randomly assigned to one of three groups: EUC, HGI or a combined Self-Help Plus and Home Gardening Intervention (SH + HGI). In the SH + HGI group, participants will receive the Self-Help Plus intervention before starting the Home Gardening Intervention.

#### Enhanced usual care

All enrolled participants will receive EUC, which consists of a single 15-min psychoeducation session with a trained assistant overseen by a qualified mental health professional, delivered before the start of the other interventions. The session is guided by a predetermined script, addressing the issue of overthinking and offering self-management techniques [46]. Participants will also receive information on utilizing existing mental health services and UNHCR partner organizations that provide psycho-social support within the refugee settlement, as well as information about a network of trained community health workers offering basic psychosocial support.

#### Home gardening intervention

The HGI is designed to promote climate-smart farming techniques, empowering participants to achieve greater self-sufficiency [24]. The intervention provides training on growing nutrient-dense crops on small plots near participants’ homes, emphasizing year-round cultivation, sustainable farming practices and knowledge transfer [47]. The HGI utilizes a four-pronged strategy: (1) supplying tools, seeds, and other essential materials; (2) offering education on home-based sustainable agricultural practices; (3) providing lessons on nutrition and cooking; and (4) teaching sustainable harvesting and market strategies.

The program starts with a 3-day training of trainers (ToT) for 20 model farmers and the monitoring team, led by senior trainers specializing in sustainable agriculture. Village-level training of the participants includes three in-person sessions with senior trainers at model farmers’ plots, each lasting approximately 6 h, with at least 2 h devoted to hands-on practice. The timing of these sessions will be staggered across the three strata. Thereafter, trained model farmers located in each village will provide continual support to participants throughout the intervention period. Each participant will receive regular in-person visits at their home garden from a model farmer or assistant monitor.

